**Quality Assurance**

Participants in the RCTs may directly benefit from their participation in the PM+ intervention, which is based on cognitive behavioural therapy (CBT) techniques (problem solving, stress management, behavioural activation, facing fears, and accessing social support) that are empirically supported and recommended by the WHO for use in low and middle income countries (Dua et al., 2011; Tol et al., 2013; WHO, 2010b). Their participation will furthermore inform local application of PM+ manual, and thus improve knowledge about delivering mental health interventions in the study area. Since PM+ is non-pharmacological and there is a broad evidence base for its use, it is unlikely that adverse effects due to the intervention will occur in Study Phases 1 and 3. Therefore, we believe that it is not necessary to install a Data Monitoring Safety Board for this study.

**Expected Outcomes of the Study**

We expect that the current study will advance knowledge about the feasibility and acceptability of implementing PM+ among women in adversity-affected communities in LAMIC. PM+ is a scalable intervention that mobilizes resources already available in settings with a lack of mental health care such as the Dagoretti Sub County, Nairobi, Kenya. PM+ is innovative in that it is simplified, low-intensity and adaptable intervention that can be delivered by supervised community health workers. Thus, it has the potential to provide the much-needed template for context-specific interventions that may not only be used in similar areas in Kenya, but rolled out to other areas for further adaptation and testing in diverse settings.

**Dissemination of Results and Publication Policy**

Results of the study will be shared with provincial and national government, county, and national health authorities have already been informed about the study, with the Kenya MoH recognised as a formal partner for the research project. In addition, all research participants will be informed about the results of the project by their community health workers.

Dissemination will also be done through World Vision to international networks in health and mental health groups to pave the way for future government and NGO partners to use these materials in other contexts.*

Results of the project will also be disseminated in English scientific peer-reviewed journals as well as in Kiswahili to key stakeholders (eg. heads of relevant health services, participants in previous community engagement meetings).

With respect to dissemination in the scientific media, we expect at least the following outputs: 1) a paper describing the qualitative assessment and the local cultural adaptation of PM+ 2) a paper describing the results of the randomised controlled trial in an international peer-reviewed journal.

An exploratory RCT to test feasibility and acceptability of PM+ in Pakistan is being carried out at the moment. Approval for this study, which is very similar to the current study, has been obtained from WHO’s Ethical Review Committee (Protocol ID RPC627). A grant proposal for a larger RCT in Pakistan has recently been submitted. In case the RCT’s show definite effectiveness of PM+ in reducing common mental health problems in Kenya, Pakistan and other low and middle income countries, it will be made widely available as part of WHO’s flagship mhGAP programme (WHO, 2010b). In addition, dissemination workshops for local health workers and policy makers would be organised.

**Duration of the Project**

|  | |
| --- | --- |
| **Study Phase 1: Exploratory randomised controlled trial** | |
| **Activities** | **Month** |
| Selection and training of CHWs (PM+ providers) and their supervisors and independent assessors | February 2014 |
| Participants are identified | March 2014 |
| Pre-intervention data are collected | April 2014 |
| CHWs (PM+ providers) implement PM+ | May-July 2014 |
| Post intervention data is collected from service users and control group | August 2014 |
|  |  |
| Control group participants who have not shown improvements are referred for PM+ | August 2014 |
| Data entry | August-Sept 2014 |
| Analysis and report of exploratory RCT results | October-Nov 2014 |
| **Study Phase 2: Process evaluation of exploratory RCT** | |
| **Activities** |  |
| Process monitoring | September 2014 |
| Qualitative interviews | September 2014 |
| **Study Phase 3: Definitive randomised controlled trial** | |
| **Activities** | **Month** |
| Pre-intervention data are collected | December 2014 |
| CHWs (PM+ providers) implement PM+ | Jan-May 2015 |
| Post intervention data is collected from service users and control group | June 2015 |
| month follow up data is collected | August 2015 |
| Control group participants who have not shown improvements are referred for PM+ | July 2015 |
| Data entry | Dec 2014 – August 2015 |
| Analysis and preparation of manuscript describing effectiveness and cost-effectiveness of PM+ in Nairobi, Kenya | August-Sept 2015 |
|  |  |
| **Study Phase 4: Process evaluation of definitive RCT** | |
| **Activities** |  |
| Process monitoring | August 2015 |
| Qualitative interviews | August 2015 |

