Data on socio-demographic information (sex, age, education, marital status and work status) will be collected through questions A1-A5 of the WHO Disability Assessment Schedule 2.0 (WHODAS; [WHO, 2010a](#_ENREF_26)), which will be administered first. The WHODAS is a generic assessment instrument assessing health and disability. It is used across all diseases, including mental neurological and substance use disorders. It is simple to administer and applicable across cultures and can be used in all adult populations. WHODAS covers six domains (cognition, mobility, self-care, getting along, life activities, participation). It assesses difficulties people have due to their illness across these domains during the last 30 days. Difficulties are scored as none, mild, moderate, severe, or extreme. We will use the 12-item interviewer administered version. The WHODAS has been validated in Kenya (Chepngeno-Langat et al., 2011).

In analyses of Study Phase 3 data, the WHODAS will also be used to compute Quality Adjusted Life years, which is a measure of disease burden, for Study Phase 3 (Buttorff et al, 2012). Reference data for the female Kenyan population will be derived from the World Health Survey, in which Kenya was included (<http://apps.who.int/healthinfo/systems/surveydata/> index.php/catalog/80).

1. GHQ-12: distress

The primary outcome is level of psychological distress as measured by the General Health Questionnaire (GHQ-12; Goldberg & Williams, 1988; Jenkins et al., 2013) at 3 months follow-up (i.e., 3 months after the 5^th^ PM+ session). The GHQ-12 consists of 12 questions that are scored on a 4-point Likert scale ranging from 0 to 3..The total GHQ-12 score is obtained by summing up the scores of the individual items and ranges between 0-36 with higher scores representing higher levels of distress. When used as a screening tool, the GHQ-12 is usually scored bi-modally (i.e. - 0-0-1-1)., and ranges between 0-12. In a previous study in Kenya, a cut-off of higher than 2 has been reported to indicate clinical levels of distress (Jenkins et al., 2013).The GHQ has been widely used across low- and middle income countries, including Kenya (Jenkins et al., 2013).

1. LEC: exposure to potentially traumatic events (life events)

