The CHWs, who will provide the PM+ intervention, already visit specific households as a standard part of their work with health facilities in the area. A local security assessment has indicated that it will be safe for screeners, assessors and CHWs to work at the household level.

All assessors and PM+ providers will receive pre-paid phone credit by the project to facilitate constant communications with each other and with the local World Vision office.

At the end of the study (at 4-5 months after inclusion), participants in the TAU condition will also be offered the PM+ intervention, if still indicated. If after the project, participants continue to experience psychological problems they will be offered additional support through aforementioned referral hospital, see above).

All adverse reactions and serious adverse events (SAEs) reported spontaneously by the subject or observed by the investigators or other staff members will be recorded by the research team. We consider an event a SAE if it is an undesirable experience occurring to a subject during the study, whether or not considered related to the research procedure. Although it is unlikely that SAEs would occur given the nature of the intervention, all adverse events and SAEs will be reported to the local independent advisory board.

The local advisory board will consist of: an independent medical officer (chair), an independent counselling psychologist with community mental health experience, the site principle investigator, and the clinical supervisor. All serious adverse events (SAE) and adverse events (AE) will be reported by the local principle investigators or supervisor to this advisory board. The chair or a nominated person from the advisory board will review SAEs within 48 hours.

Terms of reference of the advisory board are . 1. to establish rules and procedures governing its own meetings, consistent with the research protocols and standard; 2. to review SAEs within 48 hours, and all (S)AEs once a month and determine whether an (S)AE is likely to be related or unrelated to the intervention. 3 as necessary, recommend appropriate action in respect of ongoing trial conduct (such as referral to specialized care or installing extra assessment points for monitoring participants), and 4. follow-up to know whether recommended actions have taken place

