**Follow-Up**

The exploratory RCT and definitive RCT differ in follow-up assessments. While in the exploratory RCT, the final post intervention assessment by independent assessors is 1 week after the completion of PM+, in the definitive RCT the final outcome measures will be taken at 3 months after the final PM+ session. As mentioned, 5 participants will also be invited to participate in semi-structured interviews. These interviews will be conducted within 4 weeks of the final outcome assessment (i.e within 4 months of the intervention). All participants will be told that they may contact their local primary health care facility in case they need future support. Names and contact details of the field coordinator and local site PI will be provided on the consent form of which all participants receive a copy.

Depending on the adverse event, follow up may require additional tests or medical procedures as indicated, and/or referral to the general physician or a medical specialist. All adverse events will be followed until specialist care (including referrals, additional tests or medical procedures) is in place for the client, or until a stable situation has been reached.

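### The Phase 3 timetable dates referral of unimproved controls to PM+ in July 2015, one month before the August 2015 follow-up that supplies the primary GHQ-12, against the protocol's own end-of-study offer

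*Protocol*

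**What the plan says.** The Phase 3 rows of the table in Duration of the Project run as follows. Baseline: "Pre-intervention data are collected | December 2014". PM+ delivery is dated January to May 2015. Post-treatment: "Post intervention data is collected from service users and control group | June 2015". Follow-up: "month follow up data is collected | August 2015". The next row is the one at issue: "Control group participants who have not shown improvements are referred for PM+ | July 2015".

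The primary outcome is the GHQ-12 "at 3 months follow-up (i.e., 3 months after the 5^th^ PM+ session" (Methodology, Measures). The Follow-Up section agrees: "in the definitive RCT the final outcome measures will be taken at 3 months after the final PM+ session".

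Safety Considerations sets out when controls may receive the intervention: "At the end of the study (at 4-5 months after inclusion), participants in the TAU condition will also be offered the PM+ intervention", provided it is still indicated.

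**The concern.** The July row falls after the June post-treatment assessment and before the August follow-up. The women it names are chosen because they have not improved, and if follow-up is in August the only post-baseline score available to judge that in July is the June one. Taken at face value, the table moves the controls who are doing worst onto the experimental intervention before their primary outcome is recorded.

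Data Management and Statistical Analysis plans an intention-to-treat analysis, so these women would still count as TAU. If PM+ helps them, the TAU mean at 3 months improves because of PM+, and the difference between arms shrinks. Analysis cannot readily undo this, because the crossover depends on the earlier outcome.

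**Working it through.** No sample-size formula applies. The check is on dates.

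**1. What the August row is.** The numeral before the word month is missing in the text as read, but the protocol defines only one later follow-up, at 3 months. The last PM+ sessions are in May 2015, and May + 3 months = August 2015. The row is therefore the 3-month follow-up for the women treated last.

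**2. What the end of the study means for one woman.** The procedure for post-intervention assessment places that visit 7 weeks after baseline, which is 1 week after session 5.
- Session 5: 7 − 1 = 6 weeks, or 42 days after baseline.
- 3-month visit: 42 + 91 = day 133, or 19 weeks.
- In months: 133 / 30.44 = 4.4.

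This reproduces the 4 to 5 months given in Safety Considerations. The end of the study there is the 3-month follow-up, so the text leaves no room for a PM+ offer between the post-treatment visit and that follow-up.

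**3. Ordering the calendar rows.** Post-treatment June, referral July, follow-up August. Referral is at least one calendar month too early against step 2.

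**4. Could PM+ be received in the gap?** The first session is due within a week of baseline and the fifth at about week 6, so a course takes about 42 − 7 = 35 days. On the same pace, a woman starting on 1 July would finish about 5 August. A complete course before an August assessment is possible for an early starter, and a partial one for later starters.

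**5. How many could be exposed?**
- *Lower end.* Apply the per-participant schedule to the December 2014 baseline row. Baseline 1 December 2014: post-treatment visit on day 49, 19 January 2015; 3-month visit on day 133, 13 April 2015. Baseline 31 December 2014: 18 February and 13 May 2015. All 3-month visits precede July, so nobody is exposed.
- *Upper end.* Take the June, July and August rows literally for everyone. All unimproved TAU women are exposed.

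The lower-end dates also show that the calendar is only approximate, since December baselines cannot yield June post-treatment visits on a 7-week schedule.

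**6. Direction of the effect.** Let Δ be the true difference, f the fraction of TAU women who start PM+ before assessment, and g the share of the benefit they have gained by then. If the average effect is the same in these women, the intention-to-treat contrast is Δ(1 − f·g). The documents give neither f nor g, so only the direction follows, and only if PM+ works and is taken up.

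**The case against.** The strongest reply is that the operative text is already right. Safety Considerations states the order, and the table is a month-level project calendar, not a participant procedure. The table itself suggests a slip: the referral row is printed below the follow-up row, which is the correct logical order. In Phase 1 the matching row, "Control group participants who have not shown improvements are referred for PM+ | August 2014", shares the month of that trial's final assessment. Referral is also not receipt, and a month may allow only part of the course.

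Most of this stands. A dating slip is the likelier explanation, the exposure may be nil, and the size of any bias is unknown. It does not make the row correct. The protocol states no rule of precedence between the two places, and the table is the only place that gives a calendar month for referral. Phase 1 has no 3-month follow-up, so its pattern of referring straight after the post-treatment assessment could also have been carried into Phase 3 without allowing for the extra visit.

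A reader might go further and infer that the 4 to 5 month window in Safety Considerations is itself defective, because 4 × 30.44 = 122 days falls about 11 days before day 133. The document does not support that. The governing words there are the end of the study, the months are a rounded gloss, and the 3-month visit at 4.4 months lies inside them.

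**Conclusion.** The point holds as an internal contradiction. The July 2015 row in Duration of the Project precedes the August 2015 primary follow-up and conflicts with Safety Considerations, which has the order right. It should be fixed, although it is probably a slip.

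The consequence is conditional. If staff acted on the row, unimproved controls not yet seen at 3 months could begin PM+ first, and the primary contrast would tend towards no difference. This assumes that referred women take up PM+, that they receive enough of it before assessment, and that it works. Exposure lies between none and all unimproved TAU women.

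A reader might infer that contamination is planned, or that the trial loses a stated amount of power. Neither follows from the document, and no loss of power can be derived from it.

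**What to change.** Change the July 2015 cell so that referral of TAU women to PM+ comes after the 3-month follow-up, at the end of August 2015 or later. The row should make clear that each TAU woman is offered PM+ only once her own 3-month assessment is complete, which is what Safety Considerations already intends. Enhanced usual care and urgent specialist referral stay available throughout.

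The cost is one calendar entry, with no extra participants or visits. The downside is that some controls wait a few weeks longer for PM+.

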**Problems Anticipated**

We foresee no problems in completing the study phases 1, 2, 3 and 4 within the proposed time frame. Since the project group members are locally-based and are experienced in managing projects in this community.

**Ethics**

The project protocol will be reviewed by the Great Lakes University of Kenya, Nairobi and the WHO Ethics Review Committee.

No minors will be involved in this study. All participants will be adults older than 18 years.

Full information on the study will be provided in local, lay language before consent (written or oral as described above) will be obtained from each participant. This information will be read out to participants who are illiterate in the presence of a witness not affiliated with the study. We will be careful to ensure that potential participants clearly understand the implications of their involvement and that (a) they can withdraw their consent at any time without giving an explanation; (b) refusal or withdrawal of consent would have no impact upon any type of support they receive. The informed consent procedure is described in this protocol, and follows recommendations by WHO’s Ethical Review Committee (<http://www.who.int/rpc/research_ethics/Process_seeking_IF_printing.pdf>). This procedure includes: 1) oral and written information to consider participation; 2) a variant for illiterate participants, who may give consent through both a signature of a literate witness (not a member of the research team) and a thumb print.

People with recently developed, acute protection risks or recent trauma (i.e., in the past month) will be offered psychological first aid by the assessor (WHO, War Trauma Foundation and World Vision International, 2011) and linked to available support services/resources. Participants with recent trauma will also be offered psychological first aid by the assessor. All independent assessors will be trained in the Kiswahili version of the WHO, War Trauma Foundation and World Vision International (2011) guide on psychological first aid.

This study uses 5 key questions of the WHO Violence Against Women Instrument (WHO-VAW, WHO, 2003) as developed for use in the WHO Multi-Country Study on Women’s Health and Domestic Violence (WHO, 2005) and will adhere to the WHO guidelines for the conduct of violence against women research, which stress confidentiality and privacy, and availability of referral for psychological and social help. Before asking these 5 questions, women will be reminded that they are free to skip any questions. To ensure confidentiality, the interviewers are trained that of they are interrupted they will either terminate the interview, or to stop asking about violence and to move on to another, less sensitive topic until privacy can be ensured.

Another concern may involve the fact that participants in PM+ will receive treatment, whereas participants in TAU will not receive PM+. However, PM+ is a new intervention in this population, and although the efficacy of its main cognitive behavioral therapy components has been established in other populations (Dua et al., 2011; Tol et al., 2013; WHO, 2010b), a RCT is the necessary step for establishing effectiveness. In addition, participants in TAU will not be withheld care, but rather will have access to enhanced TAU. If, during the study participants in either arm of the study show severe psychiatric disorders or problems (e.g., suicidality) that require immediate treatment and follow-up, they will be referred to the relevant referral hospital.

The study is done in a low-income context, in which many individuals are exposed to multiple stressors and traumatic events. To test the utility of the PM+ protocol in real-world settings, it must be tested in situations in which it is intended to be implemented where there are ongoing stressors, uncertainty, adverse life events, etc. The current study is a necessary next step to test whether an intervention such as PM+ may be feasible and acceptable in such context with ongoing stressors and uncertainty. PM+ is based on evidence-based psychological techniques, that have been proven effective in more stable settings (WHO, 2013). Evaluating the intervention for delivery via non-specialist CHWs and testing their training and supervision procedures has to be carried out in real-life settings to provide meaningful information for implementation and scale-up.

**Informed Consent Forms**

Informed consent forms have been uploaded.

**Budget**

#### The budget has been uploaded. Note that while the trial is largely supported by Grand Challenges Canada, that World Vision Canada supports WHO’s involvement at a budget of USD 70,000

#### Other support for the project

#### None

#### Collaboration with other scientists or research institutions

#### The scientists collaborating in this project are all listed in the General Information section of this document.

#### The study involves the following institutions (see section on project management):

1. World Vision in collaboration with Ministry of Health Kenya
2. WHO.

#### All scientists, including the 2 advisors, have completed declaration of interest forms, and none have declared an interest.

#### Links to other projects

#### There is a link to the previously approved research project (Protocol ID RPC627) of WHO in collaboration with 3 Pakistan-based institutions (profs. [name], [name] and [name]) and UNSW to test the PM+ manual in Peshawar, Pakistan in an exploratory RCT

